## Abstract

Cognitive frailty (CF) is a heterogeneous syndrome that is becoming one of the most serious health problems as the world’s population age is increasing. Elucidating its biological mechanisms as well as prevention and treatments is becoming increasingly significant, particularly in view of the associated health costs. We presented the study protocol of a research project funded by the Italian Ministry of Health (grant number RF-2016-02363298) aiming to investigate the cognitive and neuropsychological effects of a 5-week treatment with therapy based on the regenerative properties of ozone (O_3_) in a cohort of subjects stratified according to CF scores. We also studied the potential effects of O_3_ on blood-based biomarkers indicative of specific biological systems that may be altered in CF. Seventy-five older persons were recruited and randomly assigned to receive the active treatment (150 cc of oxygen-O_2_-O_3_ mixture at the concentration of 30 µg of O_3_ per cc of O_2_), O_2_, or the placebo (air) for 5 weeks. The main endpoints were the change in the scores of clinical scales from baseline (T0) to weeks 3 (T3), 9 (T9), and 15 (T15) after treatment and the change in biomarker levels resulting from transcriptomics, proteomics, and metabolomic patterns at the same times. The positive results from this study could have important clinical implications.

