#### 2.1.5. Adaptive Randomization

Subjects were divided into three groups with different levels of cognitive frailty, defined according to tertiles of distribution of the scores of tests for the evaluation of memory skills (Story recall, Rey Auditory Verbal Learning Test—RAVLT immediate and delayed recall, and Rey–Osterrieth Complex Figure—ROCF Recall), attention skills (Trail Making Test part A and part B, TMT-A, TMT-B, Rey–Osterrieth Complex Figure—ROCF copy), and MMSE and GDS scores.

Participants were randomly assigned to the active treatment group (O_2_; O_2_-O_3_) or the placebo group (air), balanced for CF, so that each treatment arm accommodated a similar proportion of subjects in each tertile. The definition of the tertiles of CF was performed at different times, over a period of 12 months, on groups of 12/16 subjects, as enrollment progressed and before starting treatment. Being a double-blind study, both the researchers of the research team and the participants remained blinded to the treatment assignment until the completion of the study, while the medical doctor performing the treatment knew the treatment group, but not tertile of fragility. During recruitment, the medical doctor performing the treatment periodically re-evaluated the size of the treatment subgroups based on the recruitment and dropout rate.

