#### 2.1.7. Primary and Secondary Endpoints

The primary endpoint was the change in the scores of the clinical IFI or SHARE-Fit scales from baseline to the T3, T9, and T15 trial period after treatment.

The secondary endpoint was the change in the molecular levels (RNA and proteins) from baseline over the T3, T9, and T15 trial period after treatment.

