#### 2.2.2. Statistical Analysis

***Data analysis*.** We will present as means and standard deviations the descriptive statistics on cognitive and biological markers in the three treatment groups. The association between categorical variables will be analyzed using the Chi-square test.

The Automatic Linear Modeling (ALM) model that is based on a machine learning approach to find the best predictive model using available data will be used. A set of neuropsychological/biological values will be analyzed as independent input variables, while the scores of IFI or SHARE-FIt scales will be analyzed as continuous output (target) (dependent) variables. Longitudinal comparisons will be performed using univariate analysis, where the clinical parameters relating to the IFI and SHARE-FIt scales will be entered as dependent variables, the significant values obtained from ALM as covariates, and time and treatment as fixed factors. For the metabolomic analysis, PCA analysis (Principal Component Analysis) and a univariate analysis will be performed to evaluate the effects of the treatment on the presence/distribution of the metabolites. 

With the aim to correlate any clinical/cognitive improvements with molecular profiles to identify markers associated with response to treatment, the generalized linear mixed model (GLMM) will be used where the biological values and those relating to neuropsychological tests and the times of follow-up will be analyzed as independent input variables, while the values relating to the IFI or SHARE-FIt scales will be analyzed as weight variables and the treatments as (dependent) variables. “Air treatment” will be used as a comparison variable. All these analyses will be performed using SPSS ver. 29.

Differentially expressed genes will be identified using R-Bioconductor by applying both a fold change and p-value threshold (R-Limma test *p* value < 0.05; |Log2 fold-change ratio| > 1.0). By Fisher’s exact test, we will analyze the categories and functional pathways of upregulated or downregulated genes, using all genes in the array as the “reference” genome, or through the use of Ingenuity Pathway Analysis (IPA, Qiagen, Venlo, The Netherlands) to infer alterations in biological pathways and functions. 

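### The GLMM meant to find markers of treatment response takes randomised treatment as its outcome and the frailty scores as weights, so no term in it links improvement to a marker

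*Protocol article*

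**What the plan says.** Section 2.2.2 (Data analysis) states the purpose of the GLMM: "With the aim to correlate any clinical/cognitive improvements with molecular profiles to identify markers associated with response to treatment". The same sentence assigns every role. On the predictor side, "the biological values and those relating to neuropsychological tests and the times of follow-up will be analyzed as independent input variables". For the rest, "the values relating to the IFI or SHARE-FIt scales will be analyzed as weight variables and the treatments as (dependent) variables". The plan then adds that the air arm "will be used as a comparison variable", which fits a categorical target with air as reference. On software the section says: "All these analyses will be performed using SPSS ver. 29". It gives neither the covariance estimator nor any scaling of the weights.

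Three other places bear on this:

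- Section 2.1.5 makes treatment a randomised allocation: "Participants were randomly assigned to the active treatment group (O_2_; O_2_-O_3_) or the placebo group (air), balanced for CF". The Abstract gives the number: "Seventy-five older persons were recruited and randomly assigned", to three gases.
- Section 2.1.7 makes the frailty scales the clinical outcome: "The primary endpoint was the change in the scores of the clinical IFI or SHARE-Fit scales from baseline", to T3, T9 and T15.
- The Automatic Linear Modeling (ALM) step and the longitudinal model, both in section 2.2.2, have IFI and SHARE-FIt as dependent variables. Only the GLMM departs from this, and no other section corrects it.

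**The concern.** The question is which markers go with improvement under treatment. That needs the clinical change on one side of the model and the marker, treatment and their interaction on the other. The stated model instead predicts which gas a person received. The scales whose change defines improvement enter only as record weights, and as score levels rather than changes. Records with higher scores count more, and a record scored zero would not count at all.

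If the analysis is run as written, differences between arms could be reported as markers of response, and markers that do track improvement could be missed. Finding such markers is one of the goals that the Discussion sets for the -omics work, and it describes the correlations of molecular with clinical profiles as under way.

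**Working it through.** The plan gives no figure for this model, so there is none to reproduce. The check is the algebra of the stated model plus a simulation.

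**1. Roles in the three models of section 2.2.2**

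| Model | Dependent variable | Markers | IFI/SHARE-FIt | Treatment |
|---|---|---|---|---|
| ALM | IFI or SHARE-FIt | input | outcome | not named |
| Longitudinal | IFI, SHARE-FIt | covariate if selected by ALM | outcome | fixed factor |
| GLMM | treatment | predictor | weight | outcome |

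**2. The GLMM written out.** For subject i at visit t, with marker M, neuropsychological tests N and k = O2 or O2-O3:

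log[P(arm = k) / P(arm = air)] = a_k + b_k·M_it + c_k·N_it + d_k·t (+ subject effect),

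with each record's log-likelihood multiplied by W_it, the IFI or SHARE-FIt score.

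- W has no coefficient, so nothing estimates the relation of M to IFI or SHARE-FIt, still less to their change.
- M and N are both predictors, so nothing estimates the relation of M to cognitive change either.
- b_k asks whether M differs between arm k and air, given N and t, in a sample reweighted towards higher frailty scores.

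**3. The subject effect.** Treatment is the same at every visit, so a subject's records always agree on the target. Taking the mixed-model term to be a random subject intercept (the article does not say), its variance cannot be sensibly estimated. In a simulated two-arm check (50 subjects, 3 visits), the estimated SD collapsed to 0 with weights on a 0-1 scale and diverged when they were multiplied by 10 or 100.

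**4. What the model detects.** Inputs: 75 subjects (Abstract); visits T3, T9 and T15 (section 2.1.7); assumed 25 per arm, IFI mean about 0.2, and one marker plus time as predictors. The fit was a three-category logit without random effects, with weights normalised to mean 1 and a cluster-robust test, so the unit of the scale plays no part. There were 400 runs per row.

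| Marker shift in one arm | Correlation with IFI change | Flagged at 5% |
|---|---|---|
| 0 | 0.00 | 6.5% |
| 0 | -0.94 | 9% |
| 0.8 | 0.00 | 70% |
| 0.8 | -0.87 | 73% |

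Rows 1 and 2 differ by 2.5 points, with simulation standard error √(0.065×0.935/400 + 0.09×0.91/400) = 1.9 points. Rows 3 and 4 differ by 3 points, with standard error √(0.70×0.30/400 + 0.73×0.27/400) = 3.2 points. The arm shift drives the result, and association with improvement makes no visible difference.

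**5. Secondary: the unit of the scale.** With a categorical target the dispersion is fixed at 1. Without a random effect, multiplying all weights by c multiplies the information by c. The coefficients stay put and the model-based Wald chi-square is multiplied by c. One simulated data set (2 df, no random effect, marker coefficients -0.18 and 0.59 throughout) gave:

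| IFI expressed as | Model-based chi-square | p | Cluster-robust p |
|---|---|---|---|
| 0-1 | 3.0 | 0.22 | 0.046 |
| ×10 | 30.0 | 3e-7 | 0.046 |
| ×100 | 300 | 8e-66 | 0.046 |

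For a null marker with one record per subject and a constant weight w, the false-positive rate is P(w·χ²₂ > 5.99) = 0.05^(1/w). A mean of 0.2 rescaled ×1, ×5, ×10, ×40 and ×100 gives w = 0.2, 1, 2, 8 and 20. The rates are then 0.00003%, 5%, 22%, 69% and 86%. Simulation with varying weights gave 0%, 7%, 27%, 76% and 87%.

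The dependence vanishes with robust covariance or with normalised weights. It is weaker with a random intercept: in one simulated data set with its SD fixed at 1, z was 1.1, 2.4 and 3.5 for ×1, ×10 and ×100, against 1.1, 3.6 and 11.3 without it.

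**The case against.** The strongest reply is that the same section already has models pointing the right way. ALM predicts the frailty scales from biological and cognitive values. The longitudinal model then has the scales as outcome, the selected values as covariates, and time and treatment as factors. This stands and limits the damage. But neither model describes a marker-by-treatment term, and the response-marker aim is given to the GLMM.

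A second reply is that this is one exploratory goal of a pilot. Change in molecular levels, the secondary endpoint, has its own analyses (PCA, univariate and limma). That also stands. A reader might infer that the primary analysis or the whole -omics programme is invalid; the document does not support that.

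A third concerns units. A reader might infer that every p-value from this GLMM is arbitrary. That holds only for model-based inference with unnormalised weights. The article fixes neither choice, nor the unit in which the IFI is expressed. The chi-square figures in step 5 come from a fit without random effects and do not describe the planned mixed model.

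A fourth is that cognitive tests and visit are in the model, so improvement is not wholly absent. They are there, but beside the markers and not related to them.

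It might also be said that a separate analysis plan could settle this. The point is not a missing detail: the article states a specific model that cannot meet the aim given in the same sentence.

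**Conclusion.** The specification is wrong as written and should be corrected before any response-marker result is reported. The absence of a parameter linking improvement to a marker follows from the stated roles and rests on no simulated input. The problem with a subject random effect follows from treatment being fixed within subject, given that the mixed term is a subject effect. The 9% against 6.5%, and 70% against 73%, illustrate the consequence under assumed effect sizes, equal arms and an assumed IFI distribution. Unit dependence is a conditional, secondary defect.

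One further inference goes too far. Table 1 ticks clinical scales at baseline only, which might suggest that IFI and SHARE-FIt were not measured at follow-up. The row does not list its scales, and section 2.1.7 requires change to T3, T9 and T15. The two places conflict and must be reconciled. If only baseline scores existed, the weights would carry no information on improvement at all.

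**What to change.** Replace the GLMM sentences in section 2.2.2 with a model in the right direction:

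- **Dependent variable:** change from baseline in IFI at each follow-up visit and, in a separate model, change in SHARE-FIt.
- **Fixed effects:** treatment (air as reference), baseline (T0) marker value, marker-by-treatment, visit and baseline score.
- **Random effect:** subject intercept. No weight variable.
- **Inference:** the marker-by-treatment term identifies markers of response, with the false discovery rate controlled across markers.

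If change in a marker is used instead of its T0 value, report the result as a post-randomisation association and not as a predictor of response. If the present model is kept for any descriptive purpose, call it a comparison of markers between arms and drop the weights.

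Reconcile Table 1 with section 2.1.7 by stating at which visits IFI and SHARE-FIt were scored.

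The cost is two rewritten sentences and a corrected table row, with the same software. No new data are needed if the follow-up scores exist; if they do not, the corrected model cannot be fitted and the response-marker aim should be withdrawn for that scale.

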#### 2.2.3. Dissemination

By using peer-reviewed journals and scientific conference presentations, we will publish the results obtained from this trial to be considered by scientific investigators and healthcare professionals. The authorship requirements will adhere to the guidelines provided by the scientific journals. In addition, individual trial outcomes will be sent to participants with their consent. We will transmit the findings obtained from this study to the general population by using different and specific tools.

## 3. Discussion

This article presents the rationale and the materials/methodologies of this ongoing pilot clinical trial that has the aim of analyzing the cognitive and biological effects of O_2_-O_3_ therapy on the clinical/neuropsychological and molecular patterns in older adults with CF. This study protocol is a research project funded by the Italian Ministry of Health, grant number RF-2016-02363298. Molecular analyses and their correlations with clinical and neuropsychological profiles and with different treatments with O_2_-O_3_ therapy are currently ongoing.

Currently, specific treatments are not completely available for elderly individuals affected by CF, subjects who are potentially at risk of developing cognitive impairment and dementia. Consequently, the implementation of further potential strategic interventions may represent a useful approach to promote cognitive health and ultimately prevent cognitive decline.

O_3_ is a triatomic gaseous molecule used as a powerful oxidant in medicine for more than 150 years [38]. It has been demonstrated that O_3_ concentration and effects do not follow a linear relationship: very low concentrations could have no effect, whereas very high concentrations can lead to contrary effects to those produced by lower/middle concentrations [39]. At least 65 findings reviewed by Scassellati et al. [40] demonstrated the preconditioning/postconditioning effects of O_3_ on endogenous pro-antioxidant mechanisms in vivo on animal models and in vitro on cells. In this direction, we will test for the first time whether there is an effect of this therapy on frailty in a sample of aging subjects screened for CF scores. The rationale on which we based our hypothesis comes from some preclinical studies that demonstrated how O_3_ could be beneficent during aging through the regulation of oxidant–antioxidant homeostasis. In particular, Safwat et al. [27], performing experiments in aged rats, demonstrated that O_3_ reduced liver and kidney damage, increasing the reduced hepatic and renal glutathione (GSH) contents, as well as normalizing hepatic glutathione peroxidase (GSH-Px) enzyme activity. In another study [30], the administration of O_3_ in aged rats normalized the reduced GSH content, adenosine triphosphate/adenosine diphosphate ratio, mitochondrial superoxide dismutase (SOD), and complex IV (cytochrome-c oxidase) activities. Moreover, O_3_ improved the glutathione redox index (GSHRI), complex I (NADH-ubiquinone oxidoreductase), and mitochondrial nitric oxide synthase (mtNOS) activities and attenuated the rise in malondialdehyde (MDA) and mitochondrial phosphatidylcholine (PC) levels. In the same animal model of aged rats, another work [29] demonstrated that O_3_ decreased the lipid and protein oxidation markers as well as the lipofuscin deposition and restored both GSH levels in brain and heart tissues and GSH-Px activity in the heart tissue. O_3_ also mitigated age-associated energy failure in the heart and the hippocampus, improved cardiac cytosolic Ca(2+) homeostasis, and restored the attenuated Na(+), K(+)-ATPase activity in the hippocampus of these rats. A further study [28] demonstrated that O_3_ administration ameliorated the behavioral and pathological deterioration of APP/PS1 transgenic mice and reduced the level of amyloid-β precursor protein (APP).

By using a certificated O_3_ generator device, a gas mixture of O_2_-O_3_ obtained from the modification of medical-grade O_2_ is employed in the medical setting [41]. The therapeutic range of O_3_ has been precisely calculated, starting from the basic mechanisms of action of O_3_ in blood, and it has been found to be 10–80 μg/mL of O_3_ in blood [42]. Different and main routes of application with relative concentrations of O_3_ have been widely described by Schwart-Tapia et al. [42]. The side effects are minimal: the World Federation of Ozone therapy (WFOT) estimates the incidence of complications at 0.0007%. Moreover, given that most patients report a feeling of wellness and euphoria during the cycle of the treatment, O_3_ treatment is perfectly tolerated, and this explains why the compliance of patients remains excellent throughout the years.

To assess the frailty/CF, we used IFI as well as SHARE-FIt scales, along with CDR scores.

As reported in Sugimoto [19], there are some important issues that lead to difficulty in adapting the CF concept to clinical practice. Indeed, many studies use varied CF models and assessment tools with varied definitions of CF, making the comparison of findings across studies challenging. Therefore, a valid operational definition and an assessment tool that detect older adults at risk for reversible conditions could need to be established. Another challenge is represented by the lack of an appropriate tool for the evaluation of cognitive impairment. In this direction, we have enriched our clinical valuations by implementing a complete battery of neuropsychological tests which have been used in our trial.

The secondary endpoint of the trial is the change in biological markers levels in terms of proteomics, transcriptomics, and metabolomics. As the syndrome is multidimensional, the identification of biomarkers in CF is a complex process. In the context of the neuroimaging field, several recent papers agreed that CF is associated with loss of structure in specific brain regions such as the thalamus and hippocampus, as well as changes in white matter hyperintensity [43]. At the metabolic level, a longitudinal study performed in a population of 7769 individuals included in the Doetinchem Cohort Study [44] evidenced that markers such as high-density lipoproteins, triglycerides, alanine aminotransferase, gamma-glutamyltransferase, albumin, uric acid, cystatin C, and creatinine were not predictive of CF. Contrarily, Royal and Plamen [45] observed that the levels of insulin-like growth factor 1 and IGF-binding protein 2 levels were found to be altered in patients with cognitive decline and physical frailty. Moreover, Sargent et al. [46] reported lower levels of vitamin E alpha tocopherol, omega-6 and 3, and albumin in subjects with CF. In addition, the same authors found a further significant association with lower levels of low- and high-density lipoproteins. Finally, the focus on microbiota is a new further aspect in the development of new age-related biomarkers. For instance, He et al. [47] demonstrated that CF patients showed elevated levels of trimethylamine N-oxide, a stable metabolite of the intestinal microbiota.

In this study, we will apply a high-throughput -omic approach that will allow us to analyze the whole transcriptome and proteome in order to identify potential known as well as new biomarkers associated with the response to O_2_-O_3_ therapy treatment and, consequently, new therapeutic targets for O_3_. We thus expect that O_3_ can potentially influence biological systems linked to the immune–inflammatory system, the stress response, and oxidative stress, regeneration processes which are altered in the CF. In particular, those genes that will be differentially expressed before and after treatment and that thus will be modulated by the therapy will be verified at the biochemical level along with a panel of proteins (proteomics) that will include cytokines (i.e., IL-1β, IL-6, TNFα), immune factors (i.e., MCP-1, RANTES, MIP1), and growth factors (i.e., VEGF, BDNF, NGFβ).

These -omic approaches along with bioinformatics will allow the identification of new molecular systems involved in the etiopathogenetic mechanisms of CF and potentially new mechanisms of action for the O_3_.

This ongoing trial has some strengths. The first is the length of the study: considering the three follow-up visits in the 15 months after treatment, it was long enough to expect to have more evidence on the trajectory of cognitive changes. Second, in this study, we will include an -omics biological corollary that will permit us to potentially identify new biomarkers associated with the response to treatment with O_2_-O_3_ therapy. Moreover, this will allow us to deepen possible new mechanisms of action of the O_3_ underlying the proposed treatment-associated benefits on cognition. On the other hand, although our sample has a power effect of 0.92/0.80, the results we will obtain should be confirmed in a larger population.

